## Abstract

**Background:**

Women with type 1 diabetes strive for optimal glycemic control before and during pregnancy to avoid adverse obstetric and perinatal outcomes. For most women, optimal glycemic control is challenging to achieve and maintain. The aim of this study is to determine whether the use of real-time continuous glucose monitoring (RT-CGM) will improve glycemic control in women with type 1 diabetes who are pregnant or planning pregnancy.

**Methods/design:**

A multi-center, open label, randomized, controlled trial of women with type 1 diabetes who are either planning pregnancy with an HbA1c of 7.0 % to ≤10.0 % (53 to ≤ 86 mmol/mol) or are in early pregnancy (<13 weeks 6 days) with an HbA1c of 6.5 % to ≤10.0 % (48 to ≤ 86 mmol/mol). Participants will be randomized to either RT-CGM alongside conventional intermittent home glucose monitoring (HGM), or HGM alone. Eligible women will wear a CGM which does not display the glucose result for 6 days during the run-in phase. To be eligible for randomization, a minimum of 4 HGM measurements per day and a minimum of 96 hours total with 24 hours overnight (11 pm-7 am) of CGM glucose values are required. Those meeting these criteria are randomized to RT- CGM or HGM. A total of 324 women will be recruited (110 planning pregnancy, 214 pregnant). This takes into account 15 and 20 % attrition rates for the planning pregnancy and pregnant cohorts and will detect a clinically relevant 0.5 % difference between groups at 90 % power with 5 % significance. Randomization will stratify for type of insulin treatment (pump or multiple daily injections) and baseline HbA1c. Analyses will be performed according to intention to treat. The primary outcome is the change in glycemic control as measured by HbA1c from baseline to 24 weeks or conception in women planning pregnancy, and from baseline to 34 weeks gestation during pregnancy. Secondary outcomes include maternal hypoglycemia, CGM time in, above and below target (3.5–7.8 mmol/l), glucose variability measures, maternal and neonatal outcomes.

**Discussion:**

This will be the first international multicenter randomized controlled trial to evaluate the impact of RT- CGM before and during pregnancy in women with type 1 diabetes.

**Trial registration:**

ClinicalTrials.gov Identifier: NCT01788527 Registration Date: December 19, 2012.

**Electronic supplementary material:**

The online version of this article (doi:10.1186/s12884-016-0961-5) contains supplementary material, which is available to authorized users.

## Background

Despite all efforts, women with type 1 diabetes in pregnancy continue to have increased rates of adverse pregnancy outcomes. Women aiming for optimal glycemic control are at substantially increased risk of severe hypoglycemia (episode of low blood glucose requiring third party assistance) as well as pregnancy related complications of gestational hypertension, preeclampsia and delivery by caesarean section. Infants of mothers with diabetes face increased risk of preterm delivery, macrosomia, neonatal hypoglycemia, hyperbilirubinemia, respiratory distress and neonatal intensive care unit admissions. Macrosomia itself is associated with shoulder dystocia, birth injury, asphyxia and death. In a study of over 1,000,000 deliveries in Ontario, Canada, the rates of perinatal mortality and congenital anomalies among women with pre-existing diabetes in pregnancy were found to be approximately twice the rates of women without diabetes [1].

Numerous studies have shown that adverse pregnancy outcomes can be reduced with improved glycemic control. Pre-pregnancy care has been shown to assist women to improve glycemic control during the crucial period of organogenesis, and has been associated with reduced rates of adverse pregnancy outcomes including major congenital malformation, stillbirth and neonatal death. However, even motivated women who attend pre-pregnancy clinics still struggle to achieve and maintain optimal glycemic control [2].

CGM systems contain a subcutaneous glucose-sensing device which measures interstitial glucose and provide detailed information about the frequency and duration of glucose excursions, which is either unavailable to the user at the time of collection but available after (masked CGM) or available at the time (RT-CGM). One study comparing conventional home glucose monitoring (HGM) with masked CGM, found that CGM detected substantial hyperglycemia (>3 hours/day) and overnight hypoglycemia (1–4 hours) missed by conventional glucose monitoring [3]. Another study demonstrated that pregnant women with type 1 diabetes are still far from achieving the recommended glucose control target range of 3.9–7.8 mmol/l [4]. During the first trimester, masked CGM demonstrated that women spent 10–12 h per day hyperglycemic (>7.8 mmol/L) and 2–3 h hypoglycemic (<3.9 mmol/l). By the third trimester maternal hyperglycemia improved only slightly even with frequent antenatal clinic visits.

RT- CGM use provides additional information for the user to consider when adjusting diet, activity and insulin doses. A systematic review in non-pregnant adults, demonstrated that RT- CGM use is associated with modest improvements in glycemic control (a mean HbA1c reduction of 0.3 %), with maximal impact (up to 1.0 % reduction in HbA1c) in those with poor glycaemic control who use CGM at least 6 days per week [5]. However data from two randomized trials in pregnancy are conflicting. In a UK trial of 71 women with type 1 and type 2 diabetes, randomized to wearing a masked CGM every 4–6 weeks compared to standard care with HGM, the use of the CGM was associated with both reduced HbA1c (0.6 %) and reduced risk of macrosomia (OR 0.36, 95 % CI 0.13-0.98) [6]. A subsequent Danish trial of 154 women, randomized to use RT-CGM intermittently (six days x five times) or standard care with HGM found no difference in glycemic control or neonatal outcomes [7]. This may have been because women had good glycaemic control at baseline and were not particularly compliant with RT- CGM, with only 60 % of women using it intermittently. A systematic review thus concluded that more research is needed to identify the most effective techniques of blood glucose monitoring in pregnant women [8].

The aim of this study is to determine whether the use of continuous RT- CGM will improve glycemic control in women with type 1 diabetes who are a) planning pregnancy and b) in early in pregnancy, without substantially increasing the rate of hypoglycemia.

## Methods/design

### Overall study design

CONCEPTT is a multicenter, randomized, open label, controlled trial with an intention-to-treat analysis of two parallel trials: one trial in women planning pregnancy, and one in women in early pregnancy. Thirty trial centers are located across six countries: Canada (11), UK (15), Spain (1), Italy (1), USA (1) and Ireland (1). Women with type 1 diabetes in pregnancy who are ≤13 weeks 6 days gestation with an HbA1c of 6.5 % to ≤10.0 % (48 to ≤86 mmol/mol), and women with type 1 diabetes planning pregnancy with an HbA1c of 7.0 % to ≤10.0 % (53 to ≤86 mmol/mol), will be eligible for the run-in phase (see Fig. 1). The run-in incorporates a 6-day period during which women wear a masked CGM (Medtronic iPro®2 Professional CGM with Enlite2 sensor) to ensure that they can tolerate wearing a CGM device. Women who pass the run-in (>96 hours total with ≥24 hours overnight [11 pm-7 am] of CGM data and at least 4 HGM measurements per day) are eligible for randomization. Eligible women are randomized to CGM (Medtronic MiniMed Guardian®, Medtronic MiniMed Paradigm® Veo™ or Medtronic MiniMed® 640G system as per participant insulin delivery method) along with usual HGM, or continue HGM without CGM. The primary outcome is the change in HbA1c from baseline to 24 weeks or conception in women planning pregnancy, and from baseline to 34 weeks gestation in women who are pregnant.

**Fig. 1 Fig1:**
[figure not shown]
CONCEPTT Flow Diagram

### Primary research questions

Among women with type 1 diabetes who are planning pregnancy, does the addition of RT-CGM to HGM improve glycemic control, as measured by change in HbA1c from randomization to 24 weeks (or at conception), when compared to a standard regimen of HGM without RT-CGM?Among pregnant women with type 1 diabetes, does the addition of RT-CGM to a standard regimen of HGM improve glycemic control, as measured by change in HbA1c from randomization in early pregnancy to 34 weeks gestation (or if pregnancy loss, latest measurement), when compared to a standard regimen of HGM without RT-CGM?

### Eligibility criteria

To be eligible for the trial, participants must meet the following criteria:Clinical diagnosis of type 1 diabetes and using daily insulin therapy for at least one yearAge 18–40 yearsIntensive insulin regimen involving either an insulin pump or multiple daily injections (MDI) of insulinNo expectation that the participant will be moving out of the area during the next year

In addition, specific eligibility criteria apply for the pre-pregnant and pregnant cohorts:*Pre-pregnant cohort:*Participants are planning pregnancy and wish to optimise glycemic control before conception*Pregnant cohort:*Pregnancy gestation ≤13 weeks, 6 days at time of randomizationLive, singleton fetusUltrasound (US) done to confirm gestational age, viability and to rule out a multiple pregnancy.

Gestational age will be based on the last menstrual period (LMP) provided (±5 days discrepancy with US dates in the first trimester. If more than 5 days discrepancy from US date, or LMP not known, then US dates used).

### Exclusion criteria

Type 2 diabetesGestational diabetesRegular home user of real-time CGM in the previous 3 monthsPrevious participation in the trialEstimated GFR <60 ml/min/1.73The presence of a significant medical disorder or use of a medication such as oral glucocorticoids that in the judgment of the investigator will affect wearing of the sensors or completion of the protocol.Inpatient psychiatric treatment in the past 6 monthsParticipants using premixed fixed doses of insulin

In addition, specific exclusion criteria apply to the pre-pregnant and pregnant cohorts:*Pre-pregnancy cohort:*HbA1c <7.0 % (<53 mmol/mol) or >10.0 % (>86 mmol/mol)*Pregnancy cohort:*First HbA1c in pregnancy < 6.5 % (48 mmol/mol) or current HbA1c > 10.0 % (86 mmol/mol)Known higher order pregnancies (twins, triplets, etc.).Known fetal anomaly.

### Recruitment

Clinicians involved in the care of women with type 1 diabetes (pre-pregnant and pregnant) determine whether a patient meets the eligibility criteria and ask if she is interested in the trial. Interested patients are given a participant information sheet and time to consider taking part. Women who participate are asked to provide written informed consent prior to commencing the run-in period. Baseline data including diabetes history, current diabetes management and obstetric history are obtained. A standard physical exam (vital signs, and height and weight measurements) is performed and the participants complete validated questionnaires including the Blood Glucose Monitoring System Rating Questionnaire, the Problem Areas in Diabetes Questionnaire, the SF-12 and the Hypoglycemia Fear Survey II. UK participants are invited to complete a three day food diary.

### Run-in

The participant wears a masked CGM for 6 days. This provides a baseline assessment of glycemic control and allows participants to wear the CGM before making a decision about whether or not to continue to be randomized. The participant must test using the HGM at least 4 times per day and wear the CGM for at least 5 days, obtaining at least 96 h of glucose values and have at least 24 h of values between 23.00–07.00 h to qualify for randomization. The run-in CGM data are downloaded for evaluation by an independent data coordinating center (Jaeb Center For Health Research Inc, Tampa, Florida, USA) and not reviewed by participants or their clinicians. Should the first run-in be unsuccessful (due to insufficient CGM data), a repeat CGM can be obtained.

### Randomization

Participants who pass the run-in phase are randomized to either RT-CGM in addition to their standard HGM or HGM without CGM. The randomization process is run separately for the pre-pregnant and pregnant cohorts.

The participant’s random group assignment is determined via the Centre for Mother, Infant, and Child Research trial website. They construct a master randomization list using a permuted block design. The participants are stratified by mode of insulin therapy (pump vs. MDI) and baseline HbA1c (for pregnant group: <7.5 % or 58 mmol/mol vs. ≥7.5 % or 58 mmol/mol; for pre-pregnant group: <8.0 % or 64 mmol/mol vs. ≥8.0 % or 64 mmol/mol). Within strata, allocation are assigned in a ratio of 1:1 with random block sizes.

### Intervention

#### RT-CGM group

Participants randomized to the RT-CGM group are instructed to use the device on a daily basis. Participants are taught to insert the sensor device, perform calibration tests, use insulin dose adjustment algorithms (see Supplementary Pages for example) and to make changes to their insulin regimen based on the data from the RT-CGM and HGM. Additional HGM glucose measurements may be performed anytime, particularly prior to making management decisions based on RT-CGM values.

#### HGM group

Participants randomized to the HGM group are asked to perform at least 7 finger stick blood glucose measurements per day. Participants are taught to use insulin dose adjustment algorithms and to make changes to their insulin regimen based on data from the HGM.

#### Follow-up visits and data collection

Visits take place every 4 weeks after randomization. For the prepregnant cohort, the final visit will be at 24 weeks following randomization or at the time pregnancy is confirmed. For the pregnancy cohort, the final visit will be at 34 weeks gestation. At each visit weight, blood pressure, insulin type and dose are collected. Glucose and insulin data are reviewed along with episodes of severe hypoglycemia. Recommendations regarding diabetes management are made by treating clinicians in routine antenatal clinics. For the RT-CGM group, the RT-CGM data are downloaded and the participant’s skin is assessed. For the HGM groups, a masked CGM is used twice: for 6 days at 12 and 24 weeks in the pre-pregnant cohort and for 6 days at 24 and 34 weeks gestation in the pregnant cohort. Data from the masked CGM is downloaded to the Jaeb Center for independent review. The RT-CGM group have their RT-CGM data downloaded to the Jaeb Center for independent review 7–10 days after 12 and 24 weeks in the pre-pregnant cohort, and 24 and 34 weeks gestation in the pregnant cohort. Final questionnaires and food diaries for UK participants are repeated at 24 weeks in the pre-pregnant cohort or at time of conception, and at 34 weeks gestation in the pregnant cohort.

#### Bloods

Bloods are drawn for HbA1c at randomization, and at 12 and 24 weeks in the pre-pregnant cohort, and at 24 and 34 weeks gestation in the pregnant cohort. Biorepository bloods are drawn in those that consent, at randomization and at 34 weeks gestation for the pregnant cohort only.

#### Delivery

At delivery, cord blood is taken for blood gases (done locally) and C-peptide. If the participant consents, cord blood biorepository sample is also collected for future research. Data is collected regarding delivery and neonatal outcomes. Fetal anthropometrics are done within the first 72 h after delivery. At 6 weeks postpartum data is collected regarding neonatal wellbeing and maternal satisfaction with participating in the trial.

Women that are in the pre-pregnant cohort who become pregnant, continue in the treatment arm they were randomized to, and are followed in a similar fashion to the pregnant cohort. However, their data are analyzed separately from the pregnant cohort.

### Primary outcome

#### Pre-pregnant cohort

The primary outcome is glycemic control as measured by a change in HbA1c from randomization to 24 weeks. If the participant becomes pregnant before 24 weeks, her final HbA1c is measured post-confirmation of a positive pregnancy test.

#### Pregnant cohort

The primary outcome is glycemic control as measured by a change in HbA1c from randomization to 34 weeks gestation. In women who do not progress to 34 weeks gestation, the latest measured HbA1c is used to contribute to the primary outcome.

### Secondary outcomes

#### Pre-pregnant cohort

CGM time in target at baseline, 12 and 24 weeks.HbA1c at baseline, 12 and 24 weeks.

#### Pregnant cohort

CGM time in target at baseline, 24 and 34 weeks gestation.HbA1c at baseline, 24 and 34 weeks gestationIncidence of gestational hypertension/preeclampsiaCaesarean section: pre-labour and intrapartumGestational weight gain (randomization to 36 weeks)

#### Pre-pregnant and pregnant cohorts

Area under the curve (AUC)AUC for CGM glucose > 7.8 mmol/lAUC for CGM glucose > 6.7 mmol/lAUC for CGM glucose < 3.5 mmol/LAUC for CGM glucose < 2.8 mmol/LHypoglycemiaEpisodes of ‘severe hypoglycemia’ requiring third party assistanceMild-moderate episodes of hypoglycemia from CGM data <3.5 mmol/L (mild) and <2.8 mmol/L (moderate) for 20 min durationNocturnal hypoglycemia: CGM glucose <3.5 mmol/L (mild) and <2.8 mmol/L (moderate) for 20 min duration between 23.00–07:00 hMeasures of glucose variability:Mean amplitude of glycemic excursionsSD of CGM measurementsMean absolute rate of change of CGM based on one week of sensor valuesLength of hospital stay associated with deliveryQuestionnairesInsulin requirementsSafety outcome:A substantial increase in hypoglycemia will be defined as >10 % increase in hypoglycemic episodes (<3.5 mmol/L for at least 20 min duration) over and above the HGM group.

Infant Outcomes.Birth weight:Infant birth weight >90th centile using national growth curvesInfant birth weight >90th centile using customized centilesInfant birth weight <10th centile, using national growth curvesInfant birth weight <10th centile using customized centilesInfant birth weight ≥4 kgPregnancy loss: miscarriage, stillbirth, neonatal death (death ≤28 days of life)Preterm birth (<37 weeks and early preterm <34 weeks)Birth injuryShoulder dystociaNeonatal hypoglycemiaHyperbilirubinemiaRespiratory distressHigh level neonatal care > 24 hCord blood gas pH < 7.0Hyperinsulinemia (using cord c-peptide)Composite fetal outcome: Pregnancy loss: miscarriage, stillbirth, neonatal death (death ≤28 days of life), birth injury, neonatal hypoglycemia, hyperbilirubinemia, respiratory distress, high level neonatal care > 24 h.Sum of skin-folds >90th percentile for gestational age – triceps, sub scapular, biceps and suprailiac skin-foldsAnthropometric measures - infant birth weight, head circumference, chest circumference, abdominal circumference, left and right upper-arm circumference, crown-heel length, crown-rump lengthLength of hospital stay until first discharge home

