#### Sample size estimation

The trial will include 324 participants, with 110 in the pre-pregnant cohort (women planning pregnancy), and 214 in the pregnant cohort.

In both cohorts, the sample size is based on a clinically relevant difference in HbA1c of 0.5 %. For pregnant women, a cross-sectional standard deviation (SD) of 1.1 was used, as it is towards the upper limit of published HbA1c SD values ([9–11]. In pre-pregnant women, a SD value of 0.8 was used, based on reported SD values in a trial of CGM in young adults [12]. As this latter study also reported the SD of change over 26 weeks, it was possible to compute the correlation between repeated measurements. In the various study groups, these correlations ranged from 0.4 to 0.7. To be conservative, we used the lower value of 0.4 in our sample size calculations. In both cohorts (pre-pregnant and pregnant), sample size was computed for an analysis of covariance with the final HbA1c as the outcome and baseline HbA1c and treatment group as predictors. Power was set at 90 % and the two-tailed significance level was set at 5 %.

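### The infant sum of skin-folds is a listed outcome only as an above-90th-percentile indicator; adding the continuous sum would recover power at almost no cost

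*Protocol article*

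**What the plan says.** In the protocol article, the infant outcomes appear under Secondary outcomes, in the list headed Pre-pregnant and pregnant cohorts. The skin-fold entry is "Sum of skin-folds >90th percentile for gestational age", followed by the four sites that make up the sum. The next entry lists anthropometric measures with no threshold: birth weight, head, chest, abdominal and upper-arm circumferences, and two lengths. Skin-folds are not in that entry. Birth weight therefore appears both as centile or weight cuts and as a plain measure, while skin-folds appear only as a cut. The Delivery section says that anthropometry is done within 72 hours of birth.

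The sample size concerns HbA1c alone: "In both cohorts, the sample size is based on a clinically relevant difference in HbA1c of 0.5" %, with "Power was set at 90 % and the two-tailed significance level was set at 5" %. The Statistical analysis section describes an analysis for the primary outcome only.

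**The concern.** The indicator records whether an infant lies above the 90th percentile and nothing else. Two infants just either side of the cut count as different, and two infants far apart on the same side count as equal. A shift of the whole distribution then shows only through the few infants who cross the cut.

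The infant outcomes have whatever power a sample sized for HbA1c happens to give, so information lost in forming the outcome is not made up elsewhere. The Discussion says the trial may be able to show whether RT-CGM affects neonatal outcomes. For adiposity, the listed form makes that harder than the collected data require.

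**Working it through.** **1. The plan's own sample size.** Inputs, all from Sample size estimation unless noted:

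- "For pregnant women, a cross-sectional standard deviation (SD) of 1.1 was used", and "In pre-pregnant women, a SD value of 0.8 was used".
- Correlation between repeated measurements: "To be conservative, we used the lower value of 0.4 in our sample size calculations".
- Model: "sample size was computed for an analysis of covariance with the final HbA1c as the outcome and baseline HbA1c and treatment group as predictors".
- Allocation 1:1 (Randomization); attrition 20 % in the pregnant and 15 % in the pre-pregnant cohort (Abstract).

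The residual SD is SD × √(1 − 0.4²), and n per arm = 2 × [residual SD × (1.960 + 1.282) / 0.5]².

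- Pregnant: residual SD 1.1 × 0.917 = 1.008, so n = 85.4 per arm. Unrounded, 2 × 85.4 / 0.80 = 213.6; rounding up to 86 per arm first gives 172 / 0.80 = 215. The article states 214.
- Pre-pregnant: residual SD 0.8 × 0.917 = 0.733, so n = 45.2, or 46 per arm, and 92 / 0.85 = 108.2, or 109. The article states 110.

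Both figures reproduce to within rounding. No power is stated for skin-folds, so there is no figure to reproduce for that outcome.

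**2. Infants available.** 214 × 0.80 = 171.2, or about 86 per arm. This assumes that the attrition allowance also describes missing skin-folds.

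**3. Power on each scale.** Assume that the sum (after logs if skewed) is normal with equal spread in both arms, and that RT-CGM lowers it by d SD. Tests are two-sided at 5 %.

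- Full scale: power = Φ(d × √(n/2) − 1.96).
- Indicator: if a share p₁ of controls exceeds the cut, the RT-CGM share is p₂ = 1 − Φ(Φ⁻¹(1 − p₁) + d). Power is Φ((p₁ − p₂ − 1.96 × SE₀) / SE₁), with SE₀ from the pooled proportion and SE₁ from the two separate proportions.

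Worked case, d = 0.3, p₁ = 0.10, n = 86:

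- Full scale: 0.3 × √43 = 1.967, and Φ(1.967 − 1.96) = 50 %.
- Indicator: p₂ = 1 − Φ(1.282 + 0.3) = 0.057, difference 0.043, SE₀ = 0.0410, SE₁ = 0.0409. Power is Φ((0.043 − 0.080) / 0.0409), or 18 %.
- Loss: 32 points.

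Results with 86 per arm (losses taken before rounding):

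| Shift d (SD) | Full-scale power | Indicator power at control share 10 / 30 / 50 % | Loss in points |
|---|---|---|---|
| 0.2 | 25.8 % | 10.8 / 16.1 / 17.9 % | 15.0 / 9.7 / 8.0 |
| 0.3 | 50.3 % | 18.1 / 29.9 / 34.3 % | 32.2 / 20.4 / 16.0 |
| 0.4 | 74.6 % | 27.0 / 46.9 / 54.2 % | 47.6 / 27.8 / 20.5 |
| 0.5 | 90.6 % | 36.7 / 63.7 / 72.9 % | 53.9 / 26.9 / 17.7 |

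The 10 % share is what a 90th percentile would give if controls matched the reference population. The Background describes raised macrosomia risk in infants of mothers with diabetes, so the share may be higher; the article does not give it.

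**4. Check without a chosen shift.** For a small normal shift, the large-sample efficiency of a cut relative to the mean is φ(c)² / [p(1 − p)]. At the median this is 2/π = 64 %, the maximum. With 10 % above the cut it is 0.1755² / 0.09 = 34 %. So no placement of the cut recovers the full-scale information.

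**The case against.** The case against has four parts.

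- **Detail left to the analysis plan.** A condensed article may leave the analysis of secondary outcomes to the full protocol or SAP. This stands for the choice of model, transformation and covariates. It does not stand for the form of the skin-fold outcome, which the article states, next to a list of uncut measures that leaves skin-folds out.
- **Standardization.** The percentile is standardized for gestational age and parallels the birth-weight centile outcomes; a raw sum is not standardized. This is a good reason to keep the indicator and to adjust the continuous comparison, but not to omit the latter.
- **Cord C-peptide.** A reader might infer that it, too, is analysed only as above a cut. The article names hyperinsulinemia with C-peptide in parentheses, gives no threshold, and does not say that the concentration will not be compared. That is detail the unseen documents may hold, so the point reaches C-peptide only conditionally.
- **Size and consequence.** A reader might take the loss to be 20 points or more throughout. It is 16 to 18 points at a 50 % control share for shifts of 0.3 or 0.5 SD, and 8 to 15 points at 0.2 SD. A reader might also infer that the cut would probably turn a real effect into a null report, or that an effect of maternal glucose should be most detectable in this outcome. The documents support neither. At 0.3 SD the full-scale comparison itself has only 50 % power, and at 0.2 SD only 26 %. Nothing in the article ranks the infant outcomes by sensitivity.

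**Conclusion.** The point holds for skin-folds, as a cheap improvement to a secondary outcome. The article fixes the outcome as an indicator although the underlying measure is continuous. The loss of power is about 16 to 54 points for shifts of 0.3 to 0.5 SD and about 8 to 15 points for 0.2 SD. This assumes 86 infants per arm, a normal location shift, and 10 to 50 % of controls above the cut. Neither the shift nor the control share is in the documents, so the result is best read as a range. That some information is lost does not depend on which shift is chosen.

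This does not show an error in the sample size. The trial claims power for HbA1c only, and that calculation reproduces.

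**What to change.** Add the sum of skin-folds as a continuous secondary outcome, on the log scale if skewed. Compare the arms by linear regression adjusted for gestational age at birth, infant sex and the randomization strata, and report the mean or geometric-mean difference with a 95 % confidence interval. With this adjustment the estimate, like the percentile, is a comparison at a given gestational age. Keep the above-90th-percentile indicator alongside.

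If hyperinsulinemia is meant to be analysed only as yes or no, treat log cord C-peptide in the same way; if the concentration is already to be compared, nothing more is needed.

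The cost is wording in the outcome list and analysis text, and one extra secondary estimate (two if C-peptide is included). The values are already collected. The change should be made before outcomes are compared by arm, so that the continuous form cannot look chosen after the fact.
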